**Relavant candidate gene study**

Gene Oncology ([http://www.geneontology.org](http://www.geneontology.org/)) and the National Center for Biotechnology Information (NCBI) Gene database (<http://www.ncbi.nlm.nih.gov/gene>) and related literature to identify all functional single nucleotide polymorphisms (SNPs) of relavant genes with a minor allele frequency of more than 0.15 and a location in the promoter untranslated region or coding region of the gene.

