12.1 Sample size calculation

**Candidate gene study**

we choose type I error α = 0.05, 1-β = 0.8, two-sided test, provided the target SNP allele frequency in the population was about 20%, treatment efficacy was about 30%, OR ≥ 3.5, the calculated samples size was ≤ 86.

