**GWAS study**

We set statistical limits for the type I error α = 0.01, 1-β = 0.8, two-sided test, provided the target SNP frequency in the population > 15%, and OR> 4, according to the known lowest FOLFIRI first-line treatment induced severe adverse reactions (about 20%) and treatment efficacy (about 30%), we calculate that the needed samples will be 112 by software Quanto (Version 1.2.4), 1:1 ratio.

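### The GWAS sample size of 112 assumes equal numbers of cases and controls, but the trial is one cohort with 20–30% events, so the stated 80% power is not reached for toxicity

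*Protocol*

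**What the plan says.** Protocol section 12.1 gives two sizes.

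- **GWAS study.** "We set statistical limits for the type I error α = 0.01, 1-β = 0.8, two-sided test". The variant is assumed to have a frequency above 15% and an odds ratio above 4. The event rates are about 20% for severe adverse reactions and about 30% for efficacy. The result: "we calculate that the needed samples will be 112 by software Quanto (Version 1.2.4), 1:1 ratio".
- **Candidate gene study.** "we choose type I error α = 0.05, 1-β = 0.8, two-sided test", with an allele frequency of about 20%; then "treatment efficacy was about 30%, OR ≥ 3.5, the calculated samples size was ≤ 86". No case:control ratio is given, and toxicity is not mentioned.

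Neither paragraph names a genetic model (dominant, additive or recessive).

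The Background and the Research design section describe a prospective study. Eligible patients give blood, all receive FOLFIRI, and they are then followed for response, toxicity and survival. No step selects patients by outcome. Response and grade ≥3 adverse events are both primary endpoints. Section 12.2 plans Fisher's exact test and logistic regression, with significance at two-sided 0.05.

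**The concern.** A 1:1 ratio belongs to a case-control sample, where the investigator chooses how many patients with and without the outcome to genotype. In a cohort nobody chooses this: the split is the event rate. On the protocol's own rates, 112 patients yield 112 × 0.20 = 22 toxicity cases or 112 × 0.30 = 34 responders, not 56. Likewise 86 patients yield 86 × 0.30 = 26 responders, not 43.

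An unbalanced split carries less information per patient than a balanced one, so a total calculated at 1:1 overstates the power of the cohort. At stake is how a negative SNP result is read: a type II error of 20% is stated for a primary endpoint where the actual figure may be about twice that.

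**Working it through.** **Inputs (Protocol 12.1).** GWAS: frequency q = 0.15, OR 4, α = 0.01, event rate K = 0.20 or 0.30. Candidate gene: q = 0.20, OR 3.5, α = 0.05, K = 0.30. Power 0.80, two-sided, in both. Assumptions: Hardy-Weinberg genotypes; dominant coding first, additive as sensitivity.

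**Method.** Likelihood-ratio test of a gene-only logistic model.

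- Carrier frequency: c = 1 − (1 − q)².
- Risks p₀ (non-carriers) and p₁ (carriers) solve (1 − c)p₀ + c·p₁ = K with the stated OR.
- Carrier frequency in cases: c₁ = c·p₁/K. In controls: c₀ = c(1 − p₁)/(1 − K).
- Information per patient with case share f: δ = 2{h(f·c₁ + (1 − f)c₀) − f·h(c₁) − (1 − f)h(c₀)}, where h(x) = −x ln x − (1 − x) ln(1 − x).
- Required N = (z₁₋α/₂ + 0.842)²/δ. The numerator is (2.576 + 0.842)² ≈ 11.68 at α = 0.01 and (1.960 + 0.842)² ≈ 7.85 at α = 0.05.
- Power at n = Φ(√(nδ) − z₁₋α/₂).

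**Step 1: reproduce 112.** c = 1 − 0.85² = 0.2775. At K = 0.20: p₀ = 0.132, p₁ = 0.378, c₁ = 0.524, c₀ = 0.216. With f = 0.5, δ = 0.1043, so N = 11.68/0.1043 = 112.0, that is 56 + 56. At K = 0.30 the same 1:1 calculation gives 118, so 112 is the toxicity figure.

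**Step 2: reproduce 86.** c = 1 − 0.80² = 0.36. At K = 0.30: p₀ = 0.203, p₁ = 0.472, c₁ = 0.566, c₀ = 0.272. With f = 0.5, δ = 0.0907, so N = 7.85/0.0907 = 86.6, about 43 per group.

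Additive coding at 1:1 gives 89 (GWAS, 20%), 97 (GWAS, 30%) and 65 (candidate gene). Recessive coding gives several hundred. Of the settings tried, only dominant coding with 1:1 totals returns both stated figures.

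**Step 3: put the cohort in place of 1:1 (f = K), dominant.**

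| Study and endpoint | δ | nδ | Power | N for 80% | OR detectable with 80% power |
|---|---|---|---|---|---|
| GWAS, n = 112, toxicity 20% | 0.0698 | 7.81 | 58.7% | 168 | 5.5 |
| GWAS, n = 112, response 30% | 0.0861 | 9.65 | 70.2% | 136 | 4.6 |
| Candidate, n = 86, response 30% | 0.0774 | 6.66 | 73.2% | about 101 | 3.9 |

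First row: √7.81 − 2.576 = 0.219, and Φ(0.219) = 0.587.

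**Step 4: additive sensitivity, same cohort.** GWAS: 73% (toxicity) and 81% (response). Candidate gene: 86% (response).

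**Step 5: the planned test.** Simulated with Fisher's exact test under the dominant model (20,000 runs), power is about 55% and 67% for n = 112 (toxicity, response) and 70% for n = 86 (response), somewhat below the likelihood-ratio figures.

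**The case against.** **The genetic model is not stated.** This stands and limits the claim. A reader might infer that the design has only 59–73% power whatever the model and endpoint. The document does not support that, because additive coding puts response above 80% at both sizes. An additive cohort at 30% events would need about 110 for the GWAS, close to 112. But it would need 74, not 86, for the candidate-gene study, and it conflicts with the written 1:1 ratio. Dominant coding is therefore the better reading, not a certain one. Toxicity at n = 112 falls short under both.

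**The ratio is written only for the 112.** This stands. For the 86 both ratio and model are inferred from the reproduction. Nor does 12.1 claim power for toxicity at 86, so a shortfall there contradicts nothing written.

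**Section 12.2 tests at 0.05.** At that level 112 patients would give 79.8% (toxicity) and 87.4% (response) under the dominant model. This does not rescue the statement, since 12.1 claims its 80% at α = 0.01. It does show that the two sections must agree before a power is restated.

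**The 86 may not be an enrolment figure.** The protocol never says which size is enrolled. If 112 patients serve the candidate-gene question too, response power there is about 84% under the dominant model. So 73% applies to 86 patients, not necessarily to the study.

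**The odds ratios and the GWAS frequency are lower limits.** Larger effects or commoner variants would have more power. A power stated with a minimum effect is nevertheless a claim at that minimum.

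**More patients must be needed.** A reader might infer that 56 cases at 20% require 56/0.20 = 280 patients. They do not: the additional controls carry information, and about 168 would suffice. Restating the power requires none.

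**Conclusion.** The GWAS calculation in section 12.1 is wrong as written: it uses a 1:1 split that the described cohort cannot deliver at the protocol's own event rates. At α = 0.01 and n = 112, power for toxicity is about 59% (dominant) or 73% (additive) instead of 80%. The type II error is thus about 41% or 27%, against 20% stated. For response it is about 70% or 81%, so that shortfall depends on the dominant model.

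The point on the 86 is weaker because it rests on an inferred ratio and model: about 73% power for response (dominant), or 86% (additive).

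All figures assume Hardy-Weinberg genotypes, the stated frequencies and odds ratios at their limits, and the stated event rates.

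**What to change.** In section 12.1:

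1. Remove the 1:1 ratio, or reconcile it with the Research design section by saying how equal numbers of cases and controls would be selected.
2. State the genetic model.
3. For the GWAS, restate cohort power for both primary endpoints, or the odds ratio detectable with 80% power: about 5.5 (toxicity) and 4.6 (response) at n = 112, dominant model, α = 0.01.
4. For the candidate-gene study, do the same for response: about 73% power, or a detectable odds ratio of 3.9, at n = 86 under the dominant model. If 86 is also meant to cover toxicity, say so and give that power: 62% dominant, 79% additive.
5. Use the significance level that the analysis will apply. Section 12.1 uses 0.01 for the GWAS and section 12.2 uses 0.05; settle this first, because the restated figures depend on it.

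The cost is protocol wording and a less favourable stated figure. No added enrolment is needed.

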12.2 Statistical method

Hardy-Weinberg equilibrium will be assessed. The χ2 test will be used to compare the observed genotype frequencies with those expected under Hardy-Weinberg equilibrium.

The associations of each polymorphism with tumor response, toxicity, and demographic variables were examined using contingency tables and the Fisher’s exact test. Multivariate Logistic Regression will be performed to ascertain which genotype independently predicted response or toxicity. Odds ratios (OR) and their 95% confidence interval (CI) were calculated as estimates of the correlations. Kaplan–Meier estimates the PFS and OS. To evaluate the relationship between genotypes and PFS, IR-TTF, and OS, multivariate Cox regression (forward LR) performed, adjusting for potential confounding covariates. Hazard ratios (HR) and their 95% CI were calculated as estimates of the correlations. A value of *p* < 0.05 was considered statistically significant in a two-tailed test.

Statistical analyses were performed using SPSS16.0 (SPSS Inc, Chicago, IL) and two-sided P-value of 0.05 is considered significant.

1. **Research institutions**

Sponsor

- Tongji Hospital, Tongji Medical College, Science and Technology of Huazhong University

Collaborators

- Union Hospital, Tongji Medical College, Science and Technology of Huazhong University
- Zhongnan Hospital, Wuhan University
- Wuhan 8th Hospital, Wuhan, People’s Republic of China
- Wuhan Pu-Ai Hospital, Tongji Medical College, Huazhong University of Science and Technology
- Hubei Cancer Hospital

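### The sizes of 86 and 112 make no allowance for Fisher's exact test: if that test decides at the sizing alpha, power at a 1:1 split is about 73–75%, not 80%

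*Protocol*

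**What the plan says.** The protocol's section on objective and endpoints makes two correlations primary: SNP with objective response, and SNP with adverse events of grade 3 or higher.

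Section 12.1 sizes two studies.
- **Candidate genes:** "we choose type I error α = 0.05, 1-β = 0.8, two-sided test", with an allele frequency of about 20% and "treatment efficacy was about 30%, OR ≥ 3.5, the calculated samples size was ≤ 86". No software, case:control ratio, genetic model or test statistic is given.
- **GWAS:** "We set statistical limits for the type I error α = 0.01, 1-β = 0.8, two-sided test". The other inputs are a SNP frequency above 15%, an odds ratio above 4, and event rates of about 20% (severe toxicity) and 30% (efficacy). Then: "we calculate that the needed samples will be 112 by software Quanto (Version 1.2.4), 1:1 ratio". Again there is no genetic model or test statistic.

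Section 12.2 says that the associations of each polymorphism with response and toxicity "were examined using contingency tables and the Fisher’s exact test". It adds multivariable logistic regression for the same endpoints, to find independent predictors, with odds ratios and 95% confidence intervals. It calls neither analysis primary and sets two-sided significance at 0.05 throughout.

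**The concern.** A sample size delivers its stated power only for the test on which it was computed. Fisher's exact test is conservative in tables of this size: its true type I error sits well below nominal, and power drops with it. A size taken from a large-sample formula is therefore too small for Fisher's test.

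The test that 12.2 names for each single polymorphism is Fisher's, and 12.1 sizes exactly that situation: one SNP, one odds ratio, one binary outcome. If Fisher's test decides, a marker of just the planned strength is missed more often than the 20% that the protocol accepts. This loss belongs to the test. It remains even if the 1:1 split is taken at face value.

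**Working it through.** **Inputs from 12.1.** Candidate: allele frequency q = 0.20, OR = 3.5, event rate 0.30, alpha 0.05, N = 86. GWAS: q = 0.15, OR = 4, event rate 0.20 or 0.30, alpha 0.01, N = 112. Power 0.80, two-sided.

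**Assumptions not in the protocol.** Hardy-Weinberg genotype frequencies, a dominant model (carrier versus non-carrier), and the event rate read as the overall rate. Of the dominant, additive and recessive models, only the dominant one gives both printed sizes. A 1:1 split is stated for the GWAS and assumed for the candidate study.

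**Step 1: carrier proportions.** Carrier frequency is c = 1 − (1 − q)². The risks r0 (non-carriers) and r1 (carriers) solve (1 − c)·r0 + c·r1 = event rate with odds ratio OR. Then p1 = c·r1/rate in cases and p2 = c·(1 − r1)/(1 − rate) in controls.

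| | c | r0 | r1 | p1 | p2 |
|---|---|---|---|---|---|
| Candidate, 30% | 0.360 | 0.2033 | 0.4718 | 0.5662 | 0.2716 |
| GWAS, 20% | 0.2775 | 0.1317 | 0.3777 | 0.5241 | 0.2159 |

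Check: 0.64 × 0.2033 + 0.36 × 0.4718 = 0.30; 0.7225 × 0.1317 + 0.2775 × 0.3777 = 0.20.

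**Step 2: reproduce 86 and 112.** The pooled two-proportion formula per group, with p̄ = (p1 + p2)/2, is n = [z(α/2)·√(2p̄(1 − p̄)) + z(β)·√(p1(1 − p1) + p2(1 − p2))]² / (p1 − p2)².
- Candidate: [1.960·√0.4869 + 0.842·√0.4435]² / 0.2946² = 42.8, so 43 per group and 86 in total.
- GWAS: [2.576·√0.4662 + 0.842·√0.4187]² / 0.3082² = 55.9, so 56 per group and 112 in total.

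A large-sample 1-df likelihood-ratio calculation gives 86.6 and 112.0. Both routes match, so the printed sizes identify a large-sample calculation but not which one.

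**Step 3: exact power.** Power = Σₐ Σ_b Bin(a; n1, p1)·Bin(b; n2, p2)·1{P(a, b) ≤ α}, summed over all 2×2 tables, where P is the test's p-value.

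| 1:1 split | Large-sample (LR) | Fisher | Mid-p | LR test, exact |
|---|---|---|---|---|
| Candidate 43:43, α 0.05, 30% | 79.7% | **73.9%** | 78.1% | 81.2% |
| GWAS 56:56, α 0.01, 20% | 80.0% | **75.2%** | 79.9% | 80.9% |
| GWAS 56:56, α 0.01, 30% | 77.5% | **72.5%** | 77.6% | 78.9% |

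Fisher's true size is about 0.03 at nominal 0.05 and about 0.006 at nominal 0.01. For 80% power at 1:1, Fisher needs about 98 (candidate) and 122 (GWAS, 20%). In the last row about 2.5 of the 7.5 points missing from 80% come from the event rate and 5 from the test. Simulated 2×3 genotype tables with the exact test give about 73% (candidate) and 75% (GWAS, 20%), so the loss does not depend on collapsing to carriers.

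**Step 4: the split that the protocol's own rates imply.** 0.30 × 86 ≈ 26 cases; 0.20 × 112 ≈ 22 cases.

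| Expected split | Fisher | LR test, exact |
|---|---|---|
| Candidate 26:60, α 0.05 | 70.1% | 72.9% |
| GWAS 22:90, α 0.01 | 54.9% | 58.8% |

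**Step 5: GWAS at the alpha in 12.2.** At 0.05, Fisher's power at 56:56 with the 20% rate is 90.5%.

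**The case against.** **Fisher's test is not named as the deciding test.** This stands. Logistic regression is planned for the same endpoints, and an unadjusted likelihood-ratio test at 1:1 has about 81% power. A reader might infer that neither primary endpoint gets its 80%. The protocol supports that only if Fisher's test decides. A statistical analysis plan that is not at hand may settle this, but the protocol as written assigns the per-polymorphism tests to Fisher.

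**The documents never say likelihood-ratio.** This stands. It is tempting to say the sizes came from that test, but the pooled formula gives the same totals, so only a large-sample calculation can be claimed.

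**A planned 1:1 split is stated for the GWAS only.** This also stands, but dropping it lowers Fisher's power further.

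**The GWAS figure mixes two alphas.** This stands as a condition. The 73–75% applies at the 0.01 of 12.1. At the 0.05 of 12.2 the 1:1 figure is 90.5%, but that abandons the level on which the GWAS was sized. The candidate study uses 0.05 in both places, so its 74% needs no such condition.

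**One cohort might serve both studies.** With 112 patients, Fisher's power for the candidate inputs would be 85.1% at 56:56 and 81.8% at 34:78. The research design section does not settle this, so it cannot be relied on.

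**The inputs are rounded bounds, and 5–6 points is small beside that.** Fisher passes 80% at OR 3.9 (43:43) and OR 4.3 (56:56, alpha 0.01). True, but 80% is claimed at the limiting odds ratio. The point bears on weight, not on existence.

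**Conservatism is a legitimate choice.** It is, and Fisher's test is valid. The stated power should then be that of Fisher's test.

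**Conclusion.** The concern holds in conditional form. The sizes of 86 and 112 match large-sample calculations and contain no allowance for Fisher's exact test. If Fisher's test at the sizing alpha decides, power at 1:1 is about 74% (candidate) and 73–75% (GWAS). A candidate marker of exactly the planned strength would be missed about 26% of the time (1 − 0.739) instead of 20%. At the expected splits the figures are about 70% and 55%, where most of the extra loss comes from the imbalance and not from the test.

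This rests on the reconstructed dominant model, Hardy-Weinberg frequencies, the event rates read as overall rates, and the limiting odds ratios. The 2×2 figures are exact given these. It does not show that 80% is unattainable under every analysis that 12.2 lists. Minor to moderate severity.

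**What to change.** In 12.2, name one deciding test for the primary SNP-response and SNP-toxicity associations that matches the sizing, and state carrier coding. Two tests qualify: the 1-df likelihood-ratio test from the logistic model already planned, or the mid-p exact test.

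If Fisher's test is kept, restate the power in 12.1 for Fisher at the expected case:control split. The GWAS alpha must be reconciled between 12.1 (0.01) and 12.2 (0.05) first, because the restated figure depends on it.

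The cost is a sentence or two, with no extra patients or data. The downside is that neither replacement test guarantees a size at or below nominal. In the configurations computed at nominal 0.05, size reached about 0.051 (mid-p) and 0.054 (likelihood-ratio, 43:43, at the pooled carrier rate). Changing the test also repairs only the loss due to the test: at 26:60 and 22:90 the likelihood-ratio test still has about 73% and 59%, so the 1:1 assumption needs its own correction.

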What’s more, in different populations, genotype variants are more or less frequent. Remarkable interethnic differences in the distributions of UGT1A1 genetic polymorphisms have been known. The allele frequency of UGT1A1*28 among Caucasians is higher (0.3 to 0.4) than that among Asians (0.1 to 0.2). On the contrary, other variant alleles in the coding regions were found only in Asians.[13](#_ENREF_13)

Does Topo1 immunohistochemistry have any effect on the clinical response or prognosis for colorectal cancer patients treated with 5-FU/CPT-11 regimen? It is debated now. Some studies showed that it does not differ in TS or Topo-1 expression level in tumor.[14](#_ENREF_14) But some indicated that patients with moderate/high level of Topo-1 benefited from CPT-11.[15](#_ENREF_15) How about Topo1 gene polymorphism? Hoskins demenstrated that TOP1 and TDP1 htSNPs were related to grade 3/4 neutropenia (P = 0.04) and response (P = 0.04), respectively. [16](#_ENREF_16)But that’s not enough.

For the three limitations mentioned in the preface part, we think it is essential to carry out a prospective study in the relationship between the irinogenetics and CPT-11 toxicity, as well as the effectiveness or clinical outcome in China.

1. **Candidate genes**

- Topo1
- Carboxylesterase (CES)
- CYP3A4 cytochrome P450, family 3, subfamily A, polypeptide 4
- UGT1A1
- [ATP-binding cassette (ABC) transporters](http://en.wikipedia.org/wiki/ATP-binding_cassette_transporter)

1. **Objective and endpoints**

**Objective:** To determine the correlation between irinogenetics and irinotecan -related severe toxicities or tumor response in Chinese mCRC patients.

**Primary endpoints:** The correlation between SNP and ORR. The correlation between SNP and adverse events of Grade ≥3 (blood toxicities, diarrhea and any other serious adverse event).

**Secondary endpoints:** The correlation between SNP and PFS/OS.

1. **Research design**

Patients who meet the inclusion criteria 1-12

Record the clinical message

Collect blood samples after the consent of patients

Evaluation of target lesions

AE/toxicity

eg: diarrhe

neutropenia ect.

OS

PFS

Blood samples of each patient

Genoe-wide association study or relavant candidate gene study

The associations of each polymorphism with tumor response, toxicity, and clinical outcome (survival) will be analyzed.

1. **Method**

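### Forward-LR selection in the Cox models (Protocol 12.2) can drop the confounders those models are said to adjust for, and it overstates the hazard ratios of the genotypes it keeps

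*Protocol*

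**What the plan says.** All the relevant text is in Protocol section 12.2.

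- **Time-to-event outcomes.** The relation of genotype to PFS, IR-TTF and OS is to be examined by "multivariate Cox regression (forward LR) performed, adjusting for potential confounding covariates". No covariate is named, and nothing says that any is forced into the model.
- **Reported results.** "Hazard ratios (HR) and their 95% CI were calculated as estimates of the correlations". Significance is judged by one rule: "two-sided P-value of 0.05 is considered significant". No allowance for selection is mentioned.
- **Response and toxicity.** Each polymorphism is tested with contingency tables and Fisher's exact test. In addition, "Multivariate Logistic Regression will be performed to ascertain which genotype independently predicted response or toxicity". No entry or removal method is given for that model.

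The section on objective and endpoints places "The correlation between SNP and PFS/OS" among the secondary endpoints. ORR and grade 3 or higher adverse events are primary. IR-TTF is not a listed endpoint.

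**The concern.** Adjusting for a confounder means keeping it in the model because it is believed to matter, whatever its p-value in these data. Forward LR does the opposite: each term, covariate or genotype, has to earn its place by reaching significance in this sample. With roughly 70 to 90 events, a real prognostic factor of moderate strength will often fail. The published hazard ratio would then be described as adjusted when it is not.

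The same rule acts on the genotypes. One that enters has, by construction, an estimate far enough from 1 to pass the threshold, so the hazard ratios that reach print are those that chance pushed outward. The study wants reliable genetic markers, and exaggerated hazard ratios from a small sample are what a later study would fail to confirm.

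**Working it through.** **1. The plan's own figures.** The document gives no figure for the Cox models. It does give two sample sizes (section 12.1), used here as n. Both reproduce with a likelihood-ratio calculation for a dominant genotype in a 1:1 case-control layout: pairs = (z for two-sided alpha + z for power)² / expected LR per pair.

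- Candidate gene study (allele frequency 0.20, response 0.30, OR 3.5, alpha 0.05, power 0.80): (1.960 + 0.842)² / 0.1813 = 43.3 pairs, total 86.6, against a stated 86.
- GWAS (frequency 0.15, toxicity 0.20, OR 4, alpha 0.01, power 0.80): (2.576 + 0.842)² / 0.2085 = 56.0 pairs, total 112.0, against a stated 112.

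**2. Assumptions not in the document.** About 78% of patients have an event (67 of 86, 87 of 112); carrier frequency is 0.36 (1 − 0.8² at allele frequency 0.20); there are 5 to 20 SNPs and four covariates, one of them prognostic with HR 1.5 or 2.0; entry is at 0.05 and removal at 0.10.

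**3. Chance that a confounder misses entry, by hand.** For a binary covariate split half and half (a further assumption), expected z = √(events × 0.25) × ln(HR), and the chance of missing entry is Φ(1.96 − z).

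| Events | HR | Expected z | Chance left out |
|---|---|---|---|
| 67 | 1.5 | 4.093 × 0.405 = 1.66 | Φ(0.30) = 62% |
| 87 | 1.5 | 4.664 × 0.405 = 1.89 | Φ(0.07) = 53% |
| 67 | 2.0 | 4.093 × 0.693 = 2.84 | Φ(−0.88) = 19% |
| 87 | 2.0 | 4.664 × 0.693 = 3.23 | Φ(−1.27) = 10% |

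Simulation of the full forward procedure (600 runs per scenario) agrees: 53-64% dropped at HR 1.5 and 13-20% at HR 2.0.

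**4. Inflation of a kept genotype, by hand.** With carrier frequency 0.36, SE of ln(HR) = 1 / √(events × 0.36 × 0.64).

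- 67 events: SE = 0.2545. The smallest harmful HR that can pass is exp(1.96 × 0.2545) = 1.65.
- 87 events: SE = 0.2234. The smallest is exp(1.96 × 0.2234) = 1.55.

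Both floors lie above a true HR of 1.5, so every kept estimate in that direction is too large. The median of a normal distribution cut off at the floor is about 1.90 and 1.78. In simulation with 10 SNPs the medians when kept were 1.97 (n = 86) and 1.80 (n = 112).

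**5. The alternative under the same conditions.** With one prespecified SNP and all covariates forced in, the median HR was 1.52 and 1.47 against a true 1.5. Over all scenarios the 95% CI covered the true value in 93-96% of runs and a null SNP was rejected in 4.5-7.2%. The true SNP was significant in 34.7% and 42.0% of runs, against 34.5% and 40.7% kept by forward LR, so forcing the covariates in showed no loss of power.

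**The case against.** The strongest objection is that the choice of covariates, and whether they are held in, usually belongs to the SAP, which is not at hand. Forward selection can also be run on the genotypes alone with the covariates held in. This explains why no covariate list appears, and that absence is not the complaint. But the protocol has not left the method open: it states the selection rule and mentions no exemption for covariates.

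Four narrower objections stand and limit the point.

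- **Logistic model.** A reader might infer that response and toxicity models are also built stepwise. The text attaches forward LR to Cox only. A fixed joint logistic model, simulated without selection, rejected null SNPs at 5.5-7.1% and covered a true OR of 3.5 in 91-94% of runs, a modest departure. Its median OR did drift to 4.5-5.1 with 11 SNPs and four covariates, but that load is assumed.
- **False positives.** At least one null SNP is kept in about 41-42% of runs with 10 SNPs and 67% with 20. This is nearly all ordinary multiplicity: 1 − 0.95¹⁰ = 40% and 1 − 0.95²⁰ = 64%.
- **Coverage.** A reader might infer that intervals after selection are worthless, because kept null SNPs are covered in only 1-4% of runs. That is close to a tautology, since they were kept for being significant. For a true HR of 1.5, coverage when kept was 0.87 (n = 86) and 0.96 (n = 112).
- **Effect of a dropped confounder on false positives.** For a null SNP linked to the confounder, forward LR kept it in 5.0-8.2% of runs, against 4.5-7.2% rejected by the fixed model. The difference is small. What is lost is the adjustment: when that SNP was kept, the confounder was missing from the model in 23-75% of cases.

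**Conclusion.** The point holds for the Cox models. The sentence prescribes a procedure that does not deliver the adjustment it claims, and it yields hazard ratios for kept genotypes that are too far from 1, with nominal intervals and p-values. The sizes in the working rest on the assumed event share, carrier frequency, covariate strength and entry rule. More events or stronger confounders would reduce the dropping; fewer or weaker would increase it.

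The reach is limited to PFS and OS, which are secondary, and IR-TTF. The primary Fisher tests contain no selection step and are unaffected, as are the sample-size figures. The documents do not support extending the point to the logistic model. This should be corrected, but it does not threaten the primary analysis.

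**What to change.** Delete the forward-LR instruction from section 12.2. For each genotype, fit a Cox model with that genotype and a short set of baseline covariates already collected, chosen before the analysis and kept whatever their p-values. Report the hazard ratio and 95% CI for every genotype tested, not only the significant ones; otherwise readers who see only the significant results meet the same inflation. Label any stepwise or multi-genotype Cox model exploratory. State whether IR-TTF is an endpoint, since it appears only in this sentence.

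This does not deal with the number of SNPs tested at 0.05, which is a separate matter. The cost is a change of wording and a little more analysis. Fewer genotypes will be called independent predictors, because a stepwise model will no longer confer that label.

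### Protocol section 12.2 calls any candidate SNP significant at an uncorrected two-sided 0.05 across an unstated number of SNPs and two primary outcomes, while the sample size of 86 allows for one test

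*Protocol*

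**What the plan says.** Under Objective and endpoints, the protocol makes two kinds of association primary: SNP with ORR, and "The correlation between SNP and adverse events of Grade ≥3 (blood toxicities, diarrhea and any other serious adverse event"). The Candidate genes list has five entries: Topo1, carboxylesterase, CYP3A4, UGT1A1 and the ABC transporters. The second and the last are families. The candidate-gene part of the Method section selects all functional SNPs with minor allele frequency above 0.15 in a promoter untranslated or coding region. It does not say how many that is.

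Section 12.2 describes the analysis: "The associations of each polymorphism with tumor response, toxicity, and demographic variables were examined using contingency tables" and Fisher's exact test, followed by logistic regression. It gives the threshold twice. A p-value below 0.05 "was considered statistically significant in a two-tailed test", and again, "two-sided P-value of 0.05 is considered significant".

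Section 12.1 sizes the candidate-gene study on a single target SNP. The error rates come first: "we choose type I error α = 0.05, 1-β = 0.8, two-sided test". The other inputs are an allele frequency near 0.20, a response rate near 30% and an odds ratio of at least 3.5. The result is reported in these words: "the calculated samples size was ≤ 86".

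The protocol contains no multiplicity adjustment, no order of testing among SNPs or endpoints, and no replication set.

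**The concern.** A 0.05 threshold controls the error of one test. Here it is applied to every selected SNP and to both primary outcomes, so the chance that some SNP is wrongly declared a marker grows with the number of tests and has no stated limit. The Background gives the aim as finding reliable markers of outcome and toxicity, and these are the primary analyses, so the rule bears directly on the main conclusion.

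The threshold is also written into the plan. A later analysis plan that added a correction would change what 12.2 says; it would not be filling a gap.

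**Working it through.** **1. Does the sample size contain any allowance for multiple tests?**

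Inputs from 12.1: allele frequency 0.20, outcome rate 30%, OR 3.5, two-sided α 0.05, power 0.80. Two further inputs are assumed: a dominant model, and a 1:1 case-control layout (the protocol states that ratio only for the GWAS).

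- Carrier frequency: 1 − 0.8² = 0.36.
- Response rates giving 30% overall with OR 3.5: 0.203 in non-carriers and 0.472 in carriers.
- Carrier share: 0.36 × 0.472 / 0.30 = 0.566 in responders, and 0.36 × 0.528 / 0.70 = 0.272 in non-responders.
- Likelihood-ratio calculation with required non-centrality (1.96 + 0.84)² = 7.85: 43.3 per group, 86.6 in total.

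This matches the stated 86. The same method gives 112 for the GWAS, also as stated (α 0.01, frequency 0.15, OR 4, rate 20%). Other layouts tried do not give 86: log-additive 65, recessive 486, dominant in a cohort 101 to 102. So 86 corresponds to one test at the full 0.05.

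**2. Chance of at least one false marker**

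Assume that no SNP has an effect and that the m tests are independent. The chance is 1 − (1 − s)^m, where s is the true size of each test. The expected number of false positives at s = 0.05 is 0.05 × m.

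| Tests m | Example (SNP counts assumed) | s = 0.05 | s = 0.036 | Expected false positives at s = 0.05 |
|---|---|---|---|---|
| 10 | 5 SNPs × 2 outcomes | 0.40 | 0.31 | 0.5 |
| 14 | 7 SNPs × 2 | 0.51 | 0.40 | 0.7 |
| 20 | 10 SNPs × 2 | 0.64 | 0.52 | 1.0 |
| 30 | 15 SNPs × 2 | 0.79 | 0.67 | 1.5 |

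The chance passes one half at ln 0.5 / ln 0.95 = 13.5, so at 14 tests. Fisher's test is conservative at this sample size: simulated sizes at n = 86 were about 0.034 to 0.044. At 0.036, ln 0.5 / ln 0.964 = 18.9, so 19 tests.

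For correlated tests, correlations of 0.5 to 0.8 between SNPs in a gene and 0.3 to 0.5 between outcomes were assumed. The nominal figures then become 0.53 to 0.60 at 20 tests and 0.65 to 0.74 at 30.

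**3. What correction costs in power**

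Take a cohort of 86 with 30% response, dominant coding and OR 3.5. This layout needs 101.4 patients for 80% power, so the non-centrality at 86 is 7.85 × 86 / 101.4 = 6.66, with square root 2.58.

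- At 0.05: Φ(2.58 − 1.96) = Φ(0.62) = 0.73.
- At a Bonferroni level for 40 tests, 0.05/40 = 0.00125 with critical value 3.23: Φ(2.58 − 3.23) = Φ(−0.65) = 0.26.

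These are normal approximations; simulating Fisher's test gives about 70% and 22%. To keep 80% power on the 1:1 basis of step 1, the total rises from about 86 to about 156 for 14 tests and 175 for 30.

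**The case against.** The strongest objection concerns size. A reader might infer that at least one false marker is more likely than not. The protocol does not support that as a plain statement. It gives no SNP count, and the filter on allele frequency and location could leave few SNPs. With one SNP per listed entry and two outcomes the chance is 0.40, or 0.31 at a Fisher size of 0.036. The calculation also supposes that no SNP has any effect, while the Background reports UGT1A1 genotype as strongly associated with severe neutropenia and diarrhea. All of this stands, and it makes the figures conditional. It does not rescue the rule, since 0.31 is still about six times 0.05.

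Three other inferences go beyond the text:

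- **Three separate toxicity tests.** The parenthesis after Grade ≥3 events can equally define one composite, so two primary outcomes is the safe count.
- **Several genotype codings tried per SNP.** The protocol names no coding, but it does not plan to try several, and coding is ordinary analysis-plan content. The dominant model is a back-calculation that yields 86 only with the 1:1 layout.
- **Multiplicity explains the conflicting earlier studies.** The Background cites retrospective design, small samples, few Chinese patients and reliance on candidate genes. It does not mention multiple testing.

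It could also be said that the Research design allows a GWAS or a candidate-gene study, so the candidate tests may not be run, and that no treatment assignment depends on them. That limits the consequences, but the rule is wrong wherever the candidate route is used. Nor does the logistic regression help: it adjusts for other variables and does not control error across SNPs and endpoints.

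**Conclusion.** The point holds in conditional form. Section 12.2 fixes an uncorrected 0.05 for every candidate SNP on both primary outcomes, and the 86 in section 12.1 is consistent with one test at that level. The protocol therefore states a decision rule whose overall error is not controlled.

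How large that error is depends on a SNP count the protocol does not give. The chance of a false marker exceeds one half only from about 14 independent tests at nominal size, or about 19 at a size of 0.036, and only if every SNP is null. Correlation between tests lowers it somewhat. The defect itself does not depend on crossing one half.

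**What to change.** In 12.2, for the candidate-gene tests:

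- State the number of SNPs that pass the filter, and one pre-specified genotype coding.
- Replace the blanket 0.05 with one named procedure across all candidate SNP by primary-endpoint tests. Benjamini-Hochberg at a false discovery rate of 5% suits a marker search; Holm is the choice if family-wise control is wanted. These control different things, so the protocol should choose one and say which error it controls.
- Report SNPs that do not pass as exploratory, with unadjusted confidence intervals.
- If one SNP-outcome pair is to be tested first at full α, name a specific variant that meets the filter, and stop confirmatory testing if that test fails. Naming UGT1A1 is not enough, because it is a gene. Its *28 variant is a repeat polymorphism, and the Background gives its frequency in Asians as 0.1 to 0.2, on both sides of the 0.15 cut-off.
- In 12.1, say that the 80% power applies to one unadjusted test.

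The change is to wording only and should be made before any association results are seen. Its price is power per SNP: on the cohort basis above, from about 73% to about 26% at a Bonferroni level for 40 tests. A smaller loss is expected under false discovery rate control when several true associations exist, but that has not been quantified here.
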